### 9.2 Analysis Plan Summary

A detailed analysis plan that covers both the final analysis and the planned interim analyses will be developed and reviewed and approved internally prior to initiation of the analysis. The following is a summary of the planned analyses for the two phases. Any deviations to be made from this summary plan will be documented in the detailed analysis plan.

In Phase I, the frequency and percentage of men with procedure-related AEs will be tabulated by severity, both overall and by site. Listings of AEs will include information on duration, outcome, severity, and relation to study procedures. Listings of any serious adverse events will also be provided. Shang Ring circumcision and removal procedure data (e.g. time of circumcision and removal, problems encountered, ring sizes used) will be descriptively summarized. Data on operative and post-operative pain, time to return to normal activity, participants' opinions of the Shang Ring procedure and participants' satisfaction with the post-circumcision cosmetic results will be descriptively summarized. Time to complete wound healing will be evaluated using a Kaplan–Meier estimator.

As Phase II is a randomized study of acceptability and safety, primary analyses will be conducted using an as-treated approach (i.e., depending on anesthesia method actually received). However, any deviations between the as-treated approach and a strict intention-to-treat approach will be presented to allow for the assessment of potential biases. Some secondary analyses on safety endpoints may be repeated using an intention-to-treat approach, as relevant.

VAS pain scores will be compared between randomization groups to estimate the efficacy of anesthetic technique at the time of surgery. The frequency and percentage of men with AEs will be tabulated by randomization group, relation to study procedures, and by severity, both pooled across sites and separately within each site. The analysis of AEs will include information on duration, outcome, and relation to study procedures. Stratification by severity will also be considered.

All other endpoints will be summarized by anesthetic technique and compared between groups using either two-sample t-tests or chi-squared tests, as appropriate for the endpoint, all conducted at the two-sided 0.05 significance level. We will not make any adjustments for multiple comparisons. 95% confidence intervals for differences between groups will be presented. Missing data will be assumed to be missing in random fashion and ignored.

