Thus, in moving towards accelerated use of Shang Ring without injected anesthesia, this two-phase study will first evaluate use of the no-flip technique in an African population of males 10 years of age and older, and then in the second phase, explore topical anesthesia in a randomized study of topical vs. injected anesthesia, using the no-flip technique if it is found safe and acceptable (otherwise, the standard Shang Ring technique would be used in Phase II). The two phases may overlap as described under section 4.0 on page 17.

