Adapted from WHO Technical Advisory Group on Innovations in Male Circumcision: Evaluation of Two Adult Devices. Meeting report: Published in August 2013. Geneva, Switzerland. ISBN 978 92 4 150563 5.

Between October to December 2009, a pilot study was conducted at the Homa Bay District Hospital that sought to evaluate the safety, efficacy and acceptability of the Shang ring in the Africa population (Barone et al., 2011). This was the first use of the device outside China, and 40 adult clients were enrolled. The results showed that:

1. The Shang Ring was efficient, with short procedure times, and suitable for MC in adult men in Kenya.
2. No severe or moderate AEs were seen in this study.
3. Additionally, the device was well-tolerated, with men reporting minimal disruption to daily life and low pain scores during erections ( $3.5 \pm 2.3$ , 0=no pain and 10=worst pain possible). All men reported they were very satisfied, happy with the appearance of their circumcised penis and would recommend the Shang Ring to others .
4. This confirmed that the Shang Ring had the potential to greatly facilitate the safe and effective scale-up of MC services, especially by trained non-physicians, in settings with high HIV prevalence and low MC use.

Subsequently, between October 2010 to January 2011, we conducted a “Time to Removal” study that evaluated whether the device would spontaneously detach if removal was delayed for longer than the currently recommended time of 7 days and if wound healing was affected by different removal times (Barone et al., 2012). Fifty participants were randomized to removal of the Shang Ring at three different time points: 7, 14 and 21 days post-circumcision. The results showed that:

1. There are no serious consequences if men do not return at 7 days for removal as detachments occurred without significant problems among those who had the ring in place for more than 7 days. Complete detachment of the device occurred in 22 (66.7%) men who wore it more than 7 days.
2. Seven men (14.0%) with partial detachments requested removal 8-14 days post-circumcision due to pain or discomfort caused by the partially detached ring contacting the healing wound. Healing occurred uneventfully in these men.
3. Ring removal at later times following adult MC does not alter the time to complete healing; cumulative probabilities of complete healing were similar across groups.

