## 3.0 ENDPOINTS

### 3.1 Phase I

#### 3.1.1 Primary Endpoints

- We will address the primary objective by evaluating the rate of moderate and severe adverse eventsi (AEs) following Shang Ring MC using the no-flip technique based on clinical exam findings. Other safety endpoints will include documentation of time to complete clinical wound healing,ii device-related malfunctions and occurrences of device displacement.

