## 4.0 STUDY DESIGN

The study, to be conducted in two phases, will examine procedural and clinical outcomes, as well as participant and provider acceptability, of adaptations of the Shang Ring technique for male circumcision that would simplify its use and increase its acceptability.

- Phase I will be non-comparative for exploration of the no-flip technique for Shang Ring circumcision (i.e. all participants will be circumcised using the no-flip Shang Ring technique). Historical data from standard Shang Ring circumcisions conducted in Africa (Kenya, Uganda and Zambia) will be used as the comparison group. Men will be randomized to removal at 7 days after circumcision vs. delayed removal, to assess occurrence and safety of spontaneous detachments following circumcision with the no-flip technique.
- Phase II will compare the use of topical vs. injectable anesthesia for Shang Ring circumcision. Participants will be randomized to topical vs. injectable anesthesia in a 2:1 ratio. We rationalize the 2:1 randomization scheme given that we will have just completed Phase I in which 200 men and boys will have been circumcised using the no-flip technique with injected anesthesia. However, given the subjectivity associated with using reported pain as the primary endpoint, we believe it is critical to randomize participants in this phase of the study.

Because of the possibility that boys and men could have different outcomes after no-flip Shang Ring circumcision or could respond differently to use of topical anesthesia, we

will recruit participants equally in two age groups in both phases; 50% of participants recruited in each phase will be between 10-15 years old and the other 50% over 15 years old. Because recruitment shall be taking place at two sites, which may have different recruitment rates, and because clients need to be randomized 1:1 and 2:1 into the Phase 1 and Phase 2 treatment groups, respectively, appropriate stratified block randomization techniques by age will be applied to achieve the intended number of participants per treatment group.

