### **Phase I**

In Phase I, the Shang Ring circumcision will be completed using the no-flip technique described above for all enrolled participants. Participants will be randomized 1:1 prior to the start of the circumcision procedure to removal at 7 days or spontaneous detachment. Local anesthesia will be induced via dorsal penile nerve block (DPNB) using 1% lidocaine without epinephrine, as per WHO recommendations (WHO 2008) and Kenya national VMMC practice. This is what has been used for local anesthesia in our previous Shang Ring studies in Africa. Because of the possibility that boys and men could have different outcomes, we will recruit participants equally in two age groups; 50% ages 10-15 years old and 50% over 15 years old.

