| Day of Visit | Study procedures to be conducted                                                                                                                                                                                                                                                                                                                                                                                                                                                                |
| Day 7        | 
 
1. Remove Shang Ring
 
2. Conduct genital examination;
 
3. Examine penis and assess wound healing;
 
4. Complete relevant eCRFs;
 
5. Review AEs and SAEs, if applicable;
 
6. Review concomitant medications, if applicable;
 
7. Take penile photographs if participant agrees;
 
8. Schedule the next follow-up visit;
 
9. Reimburse participant/parent/LAR for transport costs.
 
 |
| Day 42       | 
 
1. Conduct genital examination;
 
2. Examine penis and assess wound healing;
 
3. Complete relevant eCRFs;
 
4. Review AEs and SAEs, if applicable;
 
5. Review concomitant medications, if applicable;
 
6. Take penile photographs if participant agrees;
 
7. Administer final study interview
 
8. Reimburse participant/parent/LAR for transport cost.
 
                                  |

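### The planned Phase I adverse event table pools two randomised removal schedules, so the primary no-flip rate is not like-for-like with the historical comparator or with Phase II

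*Combined protocol and SAP*

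**What the plan says.** The Phase I primary objective (section 2.1.1) is the safety of the no-flip technique. Section 3.1.1 addresses it by "evaluating the rate of moderate and severe adverse events", without naming a removal arm. Section 8.2 (Phase I) sets the allocation: "Participants will be randomized 1:1 prior to the start of the circumcision procedure to removal at 7 days or spontaneous detachment".

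The analysis summary in section 9.2 reads: "In Phase I, the frequency and percentage of men with procedure-related AEs will be tabulated by severity, both overall and by site". For Phase II, the same section does call for adverse events by randomised group.

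The comparator is given in section 4.0: "Historical data from standard Shang Ring circumcisions conducted in Africa (Kenya, Uganda and Zambia) will be used as the comparison group". Section 1.2 links Phase I to Phase II, which is to proceed "using the no-flip technique if it is found safe and acceptable (otherwise, the standard Shang Ring technique would be used in Phase II"). The Phase II day-7 task list in section 8.3 opens with "Remove Shang Ring" for all participants, whereas the Phase I list limits that step to the day-7 arm.

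Section 3.1.2 makes adverse events and healing in men who wear the ring beyond 7 days a secondary endpoint. Section 9.2 assigns that endpoint no analysis.

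**The concern.** Phase I departs from earlier practice in two ways at once: the placement technique, for everyone, and the removal schedule, for half. The primary question is about the first only. A single rate over both arms answers a different question: the risk of no-flip under an equal mix of day-7 and delayed removal. That mix is not how most historical men were treated, and it is not what Phase II will do.

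If delayed removal changes the rate of moderate or severe events, the change is credited or charged to no-flip. That could make the technique look worse than it is under day-7 removal or, if the effect ran the other way, better. The reading of Phase I also informs which technique Phase II uses, so it should be clear which schedule a finding of safe refers to.

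**Working it through.** **Inputs.**
- Phase I size: 230 enrolled, at least 200 with complete data, about 5% to be ruled out (section 9.1). No confidence level or sidedness is given; 95% is assumed below.
- Allocation 1:1 (section 8.2), hence about 100 completers per arm.
- Historical moderate adverse events: 20/1,983 = 1.0%, with no serious events (Table 2, section 12.3.1).
- Time-to-removal study (section 1.3.2): 22 men, stated as 66.7% of those wearing the ring more than 7 days, had complete detachment.

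**Step 1: the plan's own figure.** The exact (Clopper-Pearson) upper limit for x events in n men is the 1 − α quantile of Beta(x + 1, n − x), with α = 0.025 (two-sided 95%) or 0.05 (one-sided).

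| Events / n | Two-sided upper | One-sided upper |
|---|---|---|
| 3/200 | 4.32% | 3.83% |
| 4/200 | 5.04% | 4.52% |
| 5/200 | 5.74% | 5.18% |

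So 200 men exclude 5% with at most 3 events (two-sided) or 4 (one-sided). The section 9.1 statement reproduces, but for the pooled 200.

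**Step 2: how unlike the comparator the pooled sample is.** Longer wear in the historical data: 22/0.667 = 33 men, and 33/1,983 = 1.7%. In Phase I the share is 50% by design. In Phase II it is 0% by design.

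**Step 3: illustration of what pooling can do.** Let the day-7 arm have a true rate of 1% and the delayed arm a rate d, with 100 men in each. The pooled rate is (1% + d)/2. The chance of excluding 5% is P(X₁ + X₂ ≤ c), with X₁ ~ Bin(100, 0.01), X₂ ~ Bin(100, d), and c = 4 (one-sided) or 3 (two-sided).

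| d | Pooled rate | One-sided, ≤ 4/200 | Two-sided, ≤ 3/200 |
|---|---|---|---|
| 1% | 1.0% | 95% | 86% |
| 3% | 2.0% | 63% | 43% |
| 5% | 3.0% | 28% | 15% |
| 7.1% | 4.05% | 9% | 4% |
| 10% | 5.5% | 1% | 0.4% |

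The risk of no-flip with day-7 removal is 1% in every row. The values of d are assumptions. The 7.1% is 1.0% + 2/33, which supposes that both moderate events of pain leading to early removal in Table 2 came from the 33 longer wearers; the documents do not say so.

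**Step 4: precision of the day-7 arm alone.**

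| Events / n | Two-sided upper | One-sided upper |
|---|---|---|
| 0/100 | 3.62% | 2.95% |
| 1/100 | 5.45% | 4.66% |

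At a true 1%, the chance of excluding 5% is P(X ≤ 1) = 74% one-sided and P(X = 0) = 37% two-sided. The pooled sample gives 95% and 86% if delayed removal adds nothing.

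**The case against.** **No decision rule uses the pooled rate.** A reader might infer that the pooled rate, or the 5% figure, decides the Phase II technique. The documents do not say this. Sections 1.2 and 8.2 speak of safe, acceptable or positive outcomes. Section 4.0 describes a judgement in consultation with the DSMB. Section 9.1 uses 5% to justify sample size. The only explicit route to the standard technique is the interim in section 9.3, based on severe events. This stands, and it makes Step 3 an illustration under an assumed criterion.

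**The interim.** A reader might also infer that the interim and final looks describe different regimens, because the interim is triggered by 40 day-7 removals. Section 9.3 uses that count for timing and does not limit the data sent to the DSMB to those men.

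**Delayed removal may be harmless.** It is tempting to treat longer wear as a known cause of moderate or severe events, because "Seven men (14.0%) with partial detachments requested removal 8-14 days post-circumcision due to pain or discomfort". The same list in section 1.3.2 reports no serious consequences, uneventful healing in those men and no change in healing time. A request for removal is not in itself a moderate event. The direction is open.

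**The arms can be separated.** Removal time is randomised, so the day-7 rate can be recovered from the data. The secondary endpoint already requires looking at the longer wearers, and section 9.2 is a summary with a detailed plan to follow. All true: the problem lies in the planned estimate, not the data. But the secondary endpoint does not correct the primary rate, and the choice is best written down before results are seen.

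**The comparator is imperfect anyway.** Section 7.2 describes return for removal at seven to ten days under the standard technique. The historical men were adults, whereas half of Phase I is aged 10-15; the Kenyan pilot in boys, with no-flip and removal at 5-7 days, had 4 moderate events in 80 (5%). One site is new to the device. Splitting by arm removes one difference and leaves these.

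**Conclusion.** The concern holds as a gap in the planned analysis, of moderate severity. As section 9.2 is written, the primary no-flip rate combines two removal schedules in equal parts, while the historical comparator is mostly day-7 removal (about 1.7% identifiable longer wear) and Phase II is day-7 removal throughout. A comparison with historical data therefore cannot separate technique from removal time, in either direction.

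The size depends on the unknown effect of delayed removal. If there is none, pooling costs nothing and gains precision. Under the Step 3 assumptions (1% day-7 rate, 100 per arm, an exact 95% limit below 5%), a delayed-arm rate of 3% to 5% would take the pooled chance of excluding 5% from 95% to between 63% and 28% one-sided, with no change in the risk of no-flip under day-7 removal. These figures show sensitivity; they do not predict the trial's outcome. Because the allocation is randomised, this is an omission that a table can repair, not irreparable confounding.

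**What to change.** In section 9.2, or in the detailed analysis plan before data are reviewed:

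1. Tabulate Phase I moderate and severe adverse events by randomised removal arm, as well as overall and by site, with exact 95% limits and stated sidedness.
2. State that the day-7 arm is the like-for-like group for the historical comparison and for informing the Phase II technique.
3. Keep the pooled rate (about 200 men) alongside, for the 5% precision statement in section 9.1.

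The change is to wording and tables; enrolment, visits and care are untouched. The cost is precision: the day-7 arm excludes 5% with at most 1 event in 100 one-sided, or none two-sided (Step 4). Moving the 5% statement wholly to that arm would be a real trade-off, which is why the pooled rate stays for that purpose. The text should also acknowledge that age and site differences from the adult historical series remain after the split.

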#### 3.1.2 Secondary Endpoints

We will address the secondary objectives by evaluating the following endpoints:

- To evaluate ease of use with the no-flip technique we will document MC procedure and device removal times and problems encountered during MC and removal procedures;
- To evaluate satisfaction with the no-flip technique and the acceptability of wearing the Shang Ring for more than 7 days following circumcision among study participants and as appropriate their parents/LAR, we will interview participants/parents/LARs to document acceptability and satisfaction with the Shang Ring circumcision, procedure and post-procedure pain, and time to return to normal activity; and
- To evaluate satisfaction among MC providers we will interview providers to document experiences with use of the no-flip technique, problems encountered during MC procedures, and preference of MC technique.
- To determine the occurrence and safety of spontaneous detachment we will gather data on timing of spontaneous detachment and document problems/AEs and time course of complete clinical wound healing at clinical examination, as well as problems/complaints reported during interviews of participants (and as appropriate parents/LARs) among those participants wearing the Shang Ring for more than 7 days after circumcision

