| Mild AEs                                                                                                  | 43     | 2.2% (1.6%, 2.9%) |
| Anesthetic complication                                                                                   | 1      |                   |
| Pain during placement                                                                                     | 13     |                   |
| Edema                                                                                                     | 3      |                   |
| Injury                                                                                                    | 3      |                   |
| Partial detachment                                                                                        | 3      |                   |
| Bleeding                                                                                                  | 2      |                   |
| Wound disruption                                                                                          | 15     |                   |
| Insufficient skin removed                                                                                 | 3      |                   |

Adapted from WHO Technical Advisory Group on Innovations in Male Circumcision: Evaluation of Two Adult Devices. Meeting report: Published in August 2013. Geneva, Switzerland. ISBN 978 92 4 150563 5.

The figures in the above table are for Shang Ring circumcision in adults. In a study in China which involved 824 children the complication included infection (0.4%), edema (3.2%), and insufficient skin removal (0.9%). Average time for wound healing was 13.4 ± 5.8 days after circumcision (Yan, 2010). We found low rates AEs in our recently completed study of use of the Shang Ring in children in Kenya; among the 80 boys under 18 years of age who participated in the study there were no severe AEs and four moderate AEs (three cases of wound disruption, all which healed with conservative management, as well as one case of postoperative pain requiring further analgesics).

During the follow up visits, study staff will assess and provide follow-up care and/or referrals for any post-operative complications. If complications or delayed healing require longer follow-up, men will be followed by study staff as long as necessary.

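### Phase I randomizes ring removal time to study detachment safety, but the plan contains no analysis by randomized removal arm

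*Combined protocol and SAP*

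**What the plan says.** Section 4.0 gives the purpose of the Phase I randomization: "Men will be randomized to removal at 7 days after circumcision vs. delayed removal, to assess occurrence and safety of spontaneous detachments". Section 8.2 (Phase I) adds: "Participants will be randomized 1:1 prior to the start of the circumcision procedure to removal at 7 days or spontaneous detachment". Section 2.1.2 lists the occurrence and safety of spontaneous detachment as a secondary objective.

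The technique question is separate. Section 4.0 states that "Phase I will be non-comparative for exploration of the no-flip technique for Shang Ring circumcision" and that "Historical data from standard Shang Ring circumcisions conducted in Africa (Kenya, Uganda and Zambia) will be used as the comparison group".

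For the Phase I analysis, section 9.2 says that "the frequency and percentage of men with procedure-related AEs will be tabulated by severity, both overall and by site". Pain, return to activity, opinions and satisfaction are to be summarized descriptively, and healing is to be estimated by Kaplan–Meier. The removal arm is mentioned for none of these. For Phase II, the same section does tabulate adverse events by randomization group.

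Section 3.1.2 plans data on detachment timing, problems and adverse events, and healing "among those participants wearing the Shang Ring for more than 7 days after circumcision".

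**The concern.** The randomization exists to answer a safety question about longer wear, and it is the only randomized contrast in Phase I. The text then plans nothing that uses it.

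Three consequences follow:

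- **Dilution.** With a 1:1 split, an excess of adverse events in one removal arm appears in the pooled table at half its size.
- **A selected population.** The group in section 3.1.2 is defined by actual wear. It leaves out delayed-arm participants whose ring came off or was removed by day 7; section 7.2 allows removal for a problem or on request. It can take in day-7-arm participants who return late. Those excluded early may be the ones who had trouble, and no comparator is named.
- **A mixed historical contrast.** About half of Phase I is assigned to delayed removal, while the historical standard-technique cases were almost all removed earlier, as far as the protocol describes them. An excess in the pooled rate over history could come from technique or from wear time.

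**Working it through.** **Inputs**

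- Phase I size: 230 recruited, at least 200 with complete follow-up, justified as able to rule out an adverse event rate of about 5% (section 9.1).
- Allocation 1:1 (section 8.2). With equal attrition (assumption), 100 evaluable per arm.
- Historical moderate adverse events: 20/1,983 = 1.0% (Table 2, section 12.3.1).
- Removal-time study: 22 men are given as 66.7% of those wearing the ring beyond 7 days, so the denominator is 22/0.667 = 33 (section 1.3.2).
- No alpha is stated for Phase I; two-sided 0.05 is assumed. Limits are exact (Clopper–Pearson), upper limit = Beta quantile(0.975; x+1, n−x).

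**The plan's own figure.** Section 9.1 gives neither a confidence level nor an assumed true rate, so it cannot be reproduced exactly, but it is consistent with the whole cohort of 200: 3/200 has an upper limit of 4.3% and 4/200 has 5.04%. At a true rate of 1%, P(X ≤ 3 | n = 200) = 86%. Attrition also agrees: 1 − 200/230 = 13.0%.

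**Dilution by pooling (assumed rates).** Pooled rate = (p1 + p2)/2.

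| Day-7 arm | Delayed arm | Pooled | Pooled upper limit | Delayed-arm upper limit |
|---|---|---|---|---|
| 1/100 | 5/100 | 6/200 = 3% | 6.4% | 11.3% |
| 2/100 | 8/100 | 10/200 = 5% | 9.0% | 15.2% |

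**Mixing with history.** The protocol identifies 33 historical men with more than 7 days' wear. If all are in the Table 2 pool and no other study had delayed wear (assumption), that is 33/1,983 = 1.7%, against about 50% assigned to delayed removal in Phase I.

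**What a by-arm analysis can deliver.** Power of Fisher's exact test at 100 per arm, by enumeration, with 1% in the day-7 arm:

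| Delayed-arm rate | Power |
|---|---|
| 5% | 19% |
| 6.1% | 33% |
| 10% | 77% |

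Per-arm precision: 0/100 has an upper limit of 3.6%, 1/100 has 5.4% and 2/100 has 7.0%. Only zero events in an arm would rule out 5%, and at a true rate of 1% the chance of that is 0.99^100 = 37%. For the difference, 1/100 vs 5/100 gives a Newcombe 95% interval of −1.3 to +10.2 percentage points. The by-arm result is therefore estimation, not a test with adequate power for modest differences.

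**The case against.** The best defence is that Phase I is labelled non-comparative for the technique, that detachment is a secondary objective worded descriptively, that section 3.1.2 does commit to detachment data, and that section 9.2 is a summary with a detailed plan to follow. This limits the point but does not remove it. The same summary specifies analysis by randomized group for Phase II, so its absence for Phase I is a gap, and section 3.1.2 supplies neither the randomized population nor a comparator.

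Several stronger readings are tempting, and the documents do not support them:

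- **That the design confounds no-flip with delayed removal.** Everyone has no-flip and removal time is randomized within it, so the day-7 arm gives a no-flip estimate free of planned delayed removal. Only the pooled-versus-historical reading mixes the two.
- **That detachment safety goes wholly unanswered.** Section 3.1.2 gives a partial descriptive answer. Participants whose ring came off by day 7 leave only that set; their adverse events stay in the overall table and listings.
- **That delayed removal is likely to push the pooled rate past 5%.** Section 1.3.2 reports that "Seven men (14.0%) with partial detachments requested removal 8-14 days post-circumcision due to pain or discomfort". Seven of the 33 longer wearers is 21%, and one might assume a delayed-arm rate near 10%, which with 1% in the other arm pools to 5.5%. But Table 2, which covers all the African adult studies combined, has only 2 moderate events of pain leading to early removal in 1,983 placements. At most 2/33 = 6.1% of the longer wearers can fall under that heading, which with 1% pools to about 3.5%.
- **That the final pooled rate decides the Phase II technique.** No section says so. The only stated guideline (section 9.3) concerns severe adverse events at an interim look after 40 men have had rings removed at day 7; elsewhere the text refers to positive Phase I outcomes and consultation with the monitoring board.
- **That the technique comparison should rest on day-7 adults because of age differences.** Section 12.3.1 does say of Table 2 that "The figures in the above table are for Shang Ring circumcision in adults", but section 4.0 does not name Table 2 as the historical dataset. That subset would also have about 50 participants, where even 0/50 has an upper limit of 7.1% and cannot rule out 5%.

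**Conclusion.** The point holds as an omission that should be corrected. The randomized removal comparison has no planned analysis, and the population that section 3.1.2 uses in its place is formed after randomization. The pooled rate is a proper primary result for the cohort, but it cannot show a harm confined to one arm and, set against historical data, it does not separate technique from wear time.

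The size depends on arm-specific rates that are unknown. The illustration of 1% and 5% (pooled 3%, upper limit 6.4%; delayed arm alone, upper limit 11.3%) is an assumption, as are equal attrition and the two-sided 5% level. The gap in the plan does not depend on those values. Confidence is high for the omission itself; the documents do not establish that delayed removal is harmful or that any Phase II decision would change.

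**What to change.** 1. In section 9.2, add for Phase I: moderate and severe adverse events, pain, and Kaplan–Meier healing by randomized removal arm, including all randomized participants, with the adverse event risk difference and its 95% confidence interval, described as estimation.
2. In section 3.1.2, define the main population for detachment safety by randomized arm. Keep the set with more than 7 days' wear as supplementary.
3. Keep the overall adverse event rate in about 200 participants as the primary safety result, since section 9.1 sizes the whole cohort for it.
4. Show the historical comparison for the day-7 arm alone, and by age group, as supportive only.

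The cost is a few tables and some wording, with no new data or participants. The downside is precision: each arm's interval is wider than the cohort's (0/100 has an upper limit of 3.6%, against 1.8% for 0/200; 1/100 has 5.4%), and a between-arm interval that includes zero must not be read as showing equal safety.
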